## Abstract

**Background:**

Lumbar muscle strain (LMS) is a common chronic soft tissue injury disorder, and Tuina, especially Tuina rolling manipulation, is widely used for its management. However, standardized force parameters based on biomechanical effects have not yet been established, and the analgesic mechanisms of rolling manipulation remain insufficiently understood, particularly regarding its influence on cortical hemodynamic responses during manual intervention. Existing studies are fragmented, lacking systematic investigation of the entire chain from pain stimulation-induced cortical hemodynamic responses, to biomechanically optimized manipulation parameters, and to clinical efficacy. Therefore, this study aims to combine functional near-infrared spectroscopy (fNIRS) with biomechanical detection to explore cortical hemodynamic changes induced by pain stimulation, determine the optimal pressure parameters of rolling manipulation and explore the cortical hemodynamic responses associated with rolling manipulation treatment for lumbar muscle strain.

**Methods and design:**

This is a three-part, hierarchical mixed-methods study. Part 1 (Observational): We will compare cerebral hemodynamic responses (via fNIRS) between LMS patients (*n* = 15) and healthy controls (*n* = 15) under two levels of controlled pain stimulation (pain-free vs. high pain threshold). Part 2 (Interventional, Crossover): In 24 LMS patients, we will screen for the optimal pressure level (low, medium, high) of rolling manipulation by evaluating multi-dimensional biomechanical outcomes. Part 3 (Interventional, Controlled): Using the optimal pressure identified in Part 2, we will enroll 69 participants in total, including 46 patients with LMS (23 in the case intervention group and 23 in the case control group) and 23 healthy controls.fNIRS will be used to characterize cortical hemodynamic changes associated with rolling manipulation, while clinical and biomechanical outcomes will be assessed to evaluate therapeutic effects after two treatment courses.

**Discussion:**

This protocol combines neuroimaging and biomechanical assessments to explore the potential association between peripheral biomechanical responses and cortical hemodynamic changes during Tuina rolling manipulation, optimize key operational parameters, and provide preliminary evidence for future clinical research and application.

## Introduction

1

Chronic lumbar muscle strain, also known as functional low back pain, is a high-incidence musculoskeletal disease, mainly characterized by recurrent soreness and distending pain in the lumbodorsal region (1). It has become a major cause of activity limitation in the working population, and its incidence is increasing year by year and tending to be younger with the changes in modern lifestyles (2). Clinically, commonly used treatment methods included medication and physical therapy (3, 4), among which long-term medication has obvious side effects (5). Tuina therapy in traditional Chinese medicine (TCM) also belonged to physical therapy and has significant advantages. As a classic manipulation, Tuina rolling manipulation could relieve pain and improve local circulation (6, 7). However, current studies are mostly limited to symptom improvement, and the operation relies on the clinician’s clinical experience. Parameters such as pressure and frequency lacked objective quantitative standards, and there is an overall lack of research on cortical responses associated with manipulation and objective standardized mechanical parameters.

Biomechanics provided a quantitative research framework for the standardization of tuina manipulations, which analyzed the characteristics of manipulations from multiple dimensions including kinematics, dynamics and biomechanical effects (8). The stimulation dose of tuina is determined by pressure, frequency and duration, it is not the case that the greater the pressure, the better the effect (9). Excessive or insufficient pressure would affect the curative effect and even cause risks, so it is urgent to standardize the manipulation parameters to ensure safety and effectiveness (10). Kinematic studies have quantified a variety of manipulation parameters, for example, rolling manipulation has four-stage characteristics in operation, among which the operation area is large and the pressure is strong in the 1/5–1/4 time period (11). Dynamic studies have confirmed that the optimal parameter combination of rolling manipulation is a pressure of 4 kg, a frequency of 120 times/min and a duration of 10 min (12), but the quantitative research on manipulations from the perspective of biomechanical effects is still scarce. The research group has previously identified via electromyographic signals that the optimal duration of rolling manipulation for treating lumbar muscle strain was 10 min, which could relieve pain, improve dysfunction and reduce muscle tension (13).

Brain functional imaging techniques reflected the brain functional state by observing changes in brain activity, neural metabolism and hemodynamics, mainly including functional magnetic resonance imaging (fMRI) (14), positron emission tomography (PET) (15), electroencephalogram (EEG) (16), functional near-infrared spectroscopy (fNIRS) (17) and so on. Among them, fMRI has high resolution and could visualize deep brain structures but could not realize real-time detection and is expensive (18). EEG has high temporal resolution, is portable and easy to detect but has poor spatial resolution (19). As an emerging optical technology, fNIRS detects brain changes by detecting the concentration changes of oxyhemoglobin (HbO) and deoxyhemoglobin (HbR), which has the advantages of both temporal and spatial resolution, robustness against motion artifacts, portability, low cost and real-time observation, making it more suitable for the research of tuina manipulations (20, 21). Pain consisted of emotion and sensation and is closely related to the plasticity of central neurons in the brain (22, 23). Therefore, assessing pain-related cortical hemodynamic changes may provide new insights into the central responses associated with low back pain and manual interventions.fNIRS could detect the hemodynamic changes of increased HbO concentration and decreased HbR concentration under neurovascular coupling response (24), and finds that low back pain led to abnormal activation of multiple brain regions such as the dorsolateral prefrontal cortex and reduced related functional connectivity (25, 26), providing a new perspective for understanding the neural mechanism of low back pain.

At present, fNIRS is less applied in the research of tuina manipulations, and its application in the related field of TCM treatment is also scarce. Existing studies have shown that tuina at Hegu acupoint could increase the activation of the primary motor and somatosensory cortex in stroke patients, showing a certain correlation between TCM acupoints and neural circuits (27). Other studies have shown that plantar tuina could induce an increase in prefrontal HbO, suggesting that manual therapy is helpful to enhance sustained attention, verbal short-term and long-term memory (28). However, there is no report on the analysis of fNIRS brain function characteristics of tuina manipulations in the treatment of musculoskeletal diseases, and this research gap limited the in-depth understanding of the neural mechanism of tuina treatment.

### Novelty of this study

1.1

This study integrates pain-related cortical responses, biomechanical parameter optimization, and clinical evaluation to provide a systematic framework for investigating the relationship between mechanical stimulation, cortical responses, and therapeutic effects of Tuina rolling manipulation for lumbar muscle strain.Based on biomechanical effects, the optimal pressure parameters of rolling manipulation are screened to establish a quantitative correlation system of “individual pain threshold - manipulation mechanical parameters - biological effect”.fNIRS technology is first applied to monitor cortical hemodynamic responses during rolling manipulation for lumbar muscle strain, filling the technical gap in investigating cortical hemodynamic responses during TCM tuina interventions.

This study innovatively integrated multiple technologies and indicators: surface electromyography and isokinetic muscle strength are used to screen the optimal pressure parameters of rolling manipulation from the perspective of biomechanical effects and establish quantitative standards. fNIRS technology is applied to tuina research to dynamically monitor changes in cerebral blood oxygen before, during and after intervention, exploring the cortical hemodynamic responses associated with rolling manipulation in the treatment of lumbar muscle strain. fNIRS cerebral blood oxygen indicators, biomechanical indicators and clinical indicators are integrated to construct a multi-dimensional evaluation system for a comprehensive assessment of curative effect, providing a scientific basis for the standardization of rolling manipulation and the precise development of TCM tuina.

## Methods and analysis

2

### Study design and setting

2.1

This study consists of three sequential parts, including one observational component and two interventional components. The first part is an observational study aimed at comparing fNIRS-derived cortical hemodynamic responses between healthy controls and patients with lumbar muscle strain under different pain stimulation conditions. The second and third parts are interventional studies aimed at screening the optimal pressure parameters of rolling manipulation and investigating its clinical effects and associated cortical hemodynamic responses. The research setting is mainly based on the clinical testing site with functional near-infrared spectroscopy monitoring conditions and biomechanical detection equipment in the Rehabilitation Medicine Center of Yueyang Integrated Traditional Chinese and Western Medicine Hospital Affiliated to Shanghai University of Traditional Chinese Medicine. Equipment such as rapid muscle condition determinator, simulated dynamometer, surface electromyography, and isokinetic muscle strength testing system are used for data collection. Intervention methods included pain stimulation of different intensities (pain-free range and high pain threshold) and TCM rolling manipulation with graded forces (low, medium and high). This study protocol followed the SPIRIT 2013 Statement for Reporting Clinical Trial Protocols and the ethical principles proposed in the Declaration of Helsinki (2013 version). It has been approved by the Ethics Committee of Yueyang Integrated Traditional Chinese and Western Medicine Hospital Affiliated to Shanghai University of Traditional Chinese Medicine (Approval No.: 2025–197-01), all sub-centers have completed the ethical review process, and it has been registered on the International Clinical Trial Registry Platform for Traditional Medicine (Registration No.: ITMCTR2025001823). The design process is shown in Figure 1.

**Figure 1 fig1:**
[figure not shown]
Participant flow chart.

### Participants

2.2

#### Inclusion criteria

2.2.1

The research subjects of this study are divided into a case group and a control group. The case group consists of patients who met the diagnostic criteria for lumbar muscle strain in the General Principles for the Formulation and Revision of Diagnostic and Efficacy Evaluation Criteria for TCM Diseases and Syndromes (No.: ZY/T 10–2024) issued by the National Administration of Traditional Chinese Medicine in 2024 (29). The case groups in the first and third parts needed to meet the following criteria: aged 18–69 years old, regardless of gender; recurrent low back pain for more than 3 months; no other treatment for low back pain received 3 weeks before enrollment; the core area of muscle pain confirmed by physical examination is located in the lumbar erector spinae, ranging from the paravertebral region of the 12th thoracic spinous process to the dorsal surface of the sacrum and the posterior part of the iliac crest; voluntary signing of the informed consent form and cooperation in completing the entire study and providing relevant data. The second part focused on the screening of tuina manipulation pressure, so confounding factors needed to be strictly controlled, and additional requirements are made on the basis of the above criteria: aged 20–40 years old, body mass index (BMI) controlled at 18.5-24 kg/m^2^. The control group is healthy people of the same age group as the case group in the corresponding research part (18–69 years old for the first and third parts, no control group for the second part), without lumbocrural pain symptoms and a history of neuromuscular diseases, who voluntarily signed the informed consent form and cooperated in completing relevant tests.

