#### Randomization and blinding

2.3.2

Randomization is standardized in this study in combination with the design characteristics of the three parts of the experiment: The first part is a case–control observational study. After screening through strict inclusion and exclusion criteria, the case group (patients with lumbar muscle strain) and the control group (healthy people without lumbocrural pain) are selected from the eligible population by simple random sampling (15 cases in each group) to ensure sample representativeness, with no inter-group random allocation involved. The second part is a cross-over design study, in which 24 patients with lumbar muscle strain are divided into 3 groups (8 cases in each group) by complete randomization, receiving three sequences of rolling manipulation intervention with low-medium-high, medium-high-low and high-low-medium pressure, respectively. The third part is an interventional trial involving 69 participants in total. 46 patients with lumbar muscle strain are stratified by age and disease duration and then divided into a case intervention group (rolling manipulation intervention, *n* = 23) and a case control group (health education intervention, *n* = 23) by the random number table method; additionally, 23 healthy controls are selected by simple random sampling.

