#### General information collection

2.5.1

General information included age, gender, height, weight, BMI, waist-hip ratio, heart rate and medical history, smoking status, and habitual physical activity level.

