#### Primary outcome measures

2.5.2

Functional near-infrared spectroscopy (fNIRS) detection (Part 1): The primary outcome is the cortical hemodynamic response measured by fNIRS, expressed as changes in oxygenated hemoglobin (HbO) and deoxygenated hemoglobin (HbR). Measurements are obtained during the pain-free and high-pain stimulation conditions and compared with the pre-stimulation baseline. The primary comparison is between patients with LMS and healthy controls under the two stimulation conditions. We hypothesize that the cortical hemodynamic responses to pressure stimulation differ between the two groups. The fNIRS system used is a portable 49-channel system manufactured by HuiChuang (Danyang, China), consisting of 20 light sources and 16 detectors. The system uses two wavelengths of 730 and 850 nm, with a sampling rate of 11 Hz and a fixed source-detector separation of 3 cm. The probe array was positioned according to the international 10–10 system, with the D8 optode of the array aligned to the Cz position. Optode positions are recorded for each participant using a three-dimensional digitizing system and registered to Montreal Neurological Institute (MNI) space. The 49 channels cover eight predefined cortical regions: the left and right prefrontal cortex (LPFC and RPFC), left and right supplementary motor area (LSMA and RSMA), left and right primary motor cortex (LSM1 and RSM1), and left and right somatosensory association cortex (LSAC and RSAC) (Figure 2), and recorded data from participants in the static prone position and under different pain stimulations (pain-free range, VAS = 0–3; high pain threshold range, VAS = 7–10). Data preprocessing was performed using Nirspark V1.8.9 software. The preprocessing procedure included channel quality assessment, motion artifact identification and correction, band-pass filtering, conversion of optical density signals to hemoglobin concentration, and baseline correction. Channels with poor signal quality were identified according to the software-based quality control procedure and excluded from further analysis. Motion artifacts were automatically detected and corrected using the built-in motion correction algorithm, with a standard deviation threshold of 6 and amplitude threshold of 0.5. A band-pass filter (0.01–0.1 Hz) was applied to remove physiological noise and low-frequency drift. The modified Beer–Lambert law was used to calculate HbO and HbR concentrations with a differential pathlength factor (DPF) of 6. For the pain-stimulation task in Part 1, task-related hemodynamic responses are analyzed using the general linear model (GLM) implemented in NirSpark. The stimulus function is modeled using the built-in hemodynamic response function (HRF), which is defined in the software by two gamma functions separated by 2 s. The resulting β coefficients of HbO and HbR are used for subsequent analysis. For resting-state and continuous rolling-manipulation data, HbO time series are analyzed using functional connectivity, wavelet amplitude, and graph-theoretical measures. In Part 3, these analyses are used to characterize cortical hemodynamic changes before, during, and after optimal-pressure rolling manipulation.

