### Statistical analysis

2.10

Statistical analyses will be performed using MATLAB R2024b. fNIRS preprocessing and calculation of HbO/HbR concentrations, functional connectivity (FC), wavelet amplitude (WA), and graph-theoretical measures will be performed using NirSpark V1.8.9. Normally distributed continuous variables will be expressed as mean ± standard deviation, non-normally distributed variables as median and interquartile range, and categorical variables as frequencies and percentages. Normality will be assessed using the Shapiro–Wilk test. *p* < 0.05 will be considered statistically significant.

Baseline data: Baseline variables will be analyzed according to variable type, data distribution, and the number of groups using the t test, analysis of variance (ANOVA), Mann–Whitney U test, Kruskal-Wallis test, or chi-square test, as appropriate.

fNIRS data: Task-related fNIRS data will be analyzed using the general linear model (GLM) implemented in NirSpark to obtain channel-wise HbO and HbR β coefficients for subsequent group comparisons. To reduce the risk of false-positive findings arising from multiple comparisons, statistical tests of channel-wise activation will be corrected using the false discovery rate (FDR). Functional connectivity (FC), wavelet amplitude (WA), and graph-theoretical measures calculated in NirSpark will be exported for subsequent statistical analysis using linear mixed-effects models (LMM), with Bonferroni correction applied to multiple comparisons.

Biomechanical and clinical data: Repeatedly measured sEMG, muscle tension, pressure pain threshold (PPT), VAS, and ODI outcomes will be analyzed using repeated-measures ANOVA when the data are normally distributed. For non-normally distributed repeated measurements, generalized estimating equations (GEE) will be used in Parts 1 and 3, whereas the Friedman test will be used for the low-pressure, medium-pressure, and high-pressure conditions in Part 2. Bonferroni correction will be applied where multiple comparisons are required.

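### Part 1's primary patient-versus-healthy comparison is non-randomised, and controls are tied to patients only by an 18–69 age window, so age or sex can confound it

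*Protocol article*

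**What the plan says.** Section 2.5.2 defines the Part 1 primary analysis: "The primary comparison is between patients with LMS and healthy controls under the two stimulation conditions". Section 2.3.2 states that both Part 1 groups "are selected from the eligible population by simple random sampling (15 cases in each group"), "with no inter-group random allocation involved".

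Section 2.2.1 sets the eligibility of patients in Parts 1 and 3 as "aged 18–69 years old, regardless of gender". Of the controls it says: "The control group is healthy people of the same age group as the case group in the corresponding research part", and it spells this out as 18–69 for Parts 1 and 3. It sets no sex criterion for controls and no matching rule. The 23 healthy controls of Part 3 are also taken by simple random sampling (2.3.2). Section 2.4.3 compares them directly with patients on brain and biomechanical responses.

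The plan does control age elsewhere. Part 2 is restricted to ages 20–40 so as to limit confounding (2.2.1), and the randomised patients of Part 3 are stratified by age and disease duration (2.3.2).

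Age and sex will be on record: "General information included age, gender, height, weight, BMI" (2.5.1). For baseline, section 2.10 says: "Baseline variables will be analyzed according to variable type, data distribution, and the number of groups". It lists the tests but links their result to no outcome model. Section 2.7 says that baseline data are calibrated between groups, without naming a variable or a method.

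**The concern.** In a non-randomised comparison, the rule for choosing controls decides what a group difference can mean. A shared window of 69 − 18 = 51 years is an eligibility limit. It does not make the age distributions alike, and nothing ties the sex ratio of the controls to that of the patients. Simple random sampling represents each source population faithfully, so it carries over any age or sex difference between those populations.

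If cortical responsiveness to pressure also varies with age or sex, that difference appears as a patient-versus-healthy difference in HbO/HbR. The Discussion plans to read the Part 1 result as identifying cortical regions tied to pain processing in LMS. That attribution needs the groups to be comparable on such factors, or the comparison to be adjusted for them.

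Age is restricted or stratified in the two places where the design already gives protection: the within-person crossover and the randomised arms. It is left open in the comparison that has no such protection.

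**Working it through.** **Reading the selection rule.** Patients: 18–69, either sex. Controls: 18–69, sex unspecified. Both are drawn by simple random sampling with no random allocation between groups. The exclusion criteria are shared (heavy smoking, for example), but they do not balance age or sex.

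**Inputs from the article.** Section 2.8 gives 12 per group before attrition and 20% attrition: 12/(1 − 0.20) = 15 per group, as stated. Significance level 0.05.

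**Assumed inputs, not in the article.**
- Age is uniform on 18–69, so SD = 51/√12 = 14.7 years.
- The true mean age gap between the source populations is 10 years, so D = 10/14.7 = 0.68 SD. A gap of 1 SD is also shown.
- The within-group correlation r between age and response is 0.3 or 0.5.
- There is no true LMS effect.

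**Effect on an unadjusted group test.** With the response scaled to within-group SD 1, the standardised bias is r × D and the noncentrality is r × D × √(n/2), with √(15/2) = 2.74.
- r = 0.3, D = 0.68: bias 0.20, noncentrality 0.56
- r = 0.5, D = 0.68: bias 0.34, noncentrality 0.93

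Rejection rates at a nominal 5%, 15 per group. The simulation has 4000 runs, so its standard error near 5% is √(0.05 × 0.95/4000) = 0.34 percentage points:

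| D (SD) | r | Unadjusted, noncentral t | Unadjusted, simulated | Age as covariate, simulated |
|---|---|---|---|---|
| 0.68 | 0.3 | 8.4% | 8.5% | 4.5% |
| 0.68 | 0.5 | 14.7% | 14.3% | 4.8% |
| 1.0 | 0.3 | 12.5% | 13.0% | 5.0% |
| 1.0 | 0.5 | 26.2% | 25.7% | 5.2% |

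**Can the baseline test be relied on to reveal the gap?** For a two-sample t test with 28 degrees of freedom, the noncentrality for a 10-year gap is 0.68 × 2.74 = 1.86, against a critical value of 2.05.
- SD 14.7: power 44% (36% if only 12 per group remain)
- SD 12: power 60%
- SD 10: power 75%

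At SD 10 the gap is easier to detect, but it is then 1 SD, so the lower half of the table applies. A non-significant baseline test is therefore weak reassurance.

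**Scope of the illustration.** It covers age alone and a single group comparison. It does not model sex, or the false discovery rate correction across channels in section 2.10.

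**The case against.** The strongest reply is that much of what looks missing may be in a document that is not shown. Section 2.10 gives no full model specification, and silence on covariates does not exclude them. That stands: a reader might infer that age and sex will be left out of the analysis, and the article does not say so. It does state how controls are chosen, and that rule contains no matching.

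The design also has partial safeguards. Part 1 responses are compared with each participant's own baseline, and pressures are set individually by VAS. This removes additive differences in level between people, but not an age-dependent difference in responsiveness. Section 2.7 says baseline data are calibrated, but with no variable or method named this cannot be counted as matching. The article states openly that Part 1 is observational, and it describes its evidence as preliminary.

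Three further inferences are tempting, and the article does not support them:

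- **Controls will be younger.** Section 2.3.1 describes outpatient departments and social media announcements for participants in general. It assigns no separate route to patients and controls.
- **Chance imbalance at 15 per group is itself a bias.** If both groups came from the same age distribution, chance gaps would be covered by the test's error rate. Confounding needs a systematic difference.
- **The fixed optical path setting adds an age bias.** Section 2.5.2 converts signals "with a differential pathlength factor (DPF) of 6", but the article gives no dependence of that factor on age.

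**Conclusion.** The point holds as a weakness in the stated selection rule. Part 1's primary contrast, and the patient-versus-healthy comparison in Part 3, can be confounded by age or sex because nothing in the article makes the groups alike on either. The randomised ODI comparison is not affected.

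The article supports only that confounding can occur. It does not show that it will, and it gives no size for an age gap, a sex imbalance or an age effect on HbO/HbR. Under the assumed 10-year gap and correlations of 0.3 to 0.5, the false-positive rate rises from 5% to about 8.5–14%, adjustment for age brings it back to about 5%, and the baseline t test would detect the gap about 44% of the time. With a gap of 1 SD the rate is about 13–26%. If the source populations do not differ in age or sex, the inflation disappears.

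This should be changed but does not invalidate the trial. The matching part has to be settled before controls are recruited.

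**What to change.** In sections 2.2.1 and 2.3.2, replace simple random sampling of healthy controls in Parts 1 and 3 with frequency matching to the enrolled patients by sex and a coarse age split. Two bands by sex give 4 cells for 15 controls and three bands give 6, so nothing finer is practical in Part 1.

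In section 2.10, prespecify age and sex as covariates in the primary Part 1 group comparison and in the Part 3 patient-versus-healthy comparisons, whatever the baseline p-values. In section 2.7, either define how baseline data are calibrated between groups or delete the statement.

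Cost: two degrees of freedom per model and somewhat slower control recruitment, since controls must fill quotas set by the patients already enrolled. Both variables are already collected, so no new measurement is needed.

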#### Exclusion criteria

2.2.2

The contents of the case group and the control group are consistent, and the three parts of the experiment are identical, except that Item (h) is absent in the second part. (a) Patients with mental disorders or impaired consciousness; (b) Pregnant, lactating women and women preparing for pregnancy; (c) Heavy smokers, defined as those smoking at least 20 cigarettes (1 pack) per day; (d) Complicated with non-soft tissue chronic injury diseases such as lumbar intervertebral disc herniation, spinal stenosis and intraspinal lesions; (e) Pain caused by lumbar spine surgery, trauma, rheumatoid arthritis, etc.; (f) Malignant tumors, acute infectious diseases, severe skin diseases, rheumatism and immune diseases, complicated with severe heart, liver and kidney diseases; (g) Patients participating in other external therapies, medications and other treatments that may affect the judgment of results; (h) Contraindications to fNIRS monitoring such as a history of craniocerebral surgery, cranial defects and phobia of headgear wearing.

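### A history of neuromuscular disease excludes healthy controls but not patients, so the Part 1 primary fNIRS contrast applies this one criterion to one group only

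*Protocol article*

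**What the plan says.** Section 2.2.1 defines the two groups separately. For Parts 1 and 3, patients must meet a national diagnostic standard for lumbar muscle strain, be aged 18 to 69, and have "recurrent low back pain for more than 3 months; no other treatment for low back pain received 3 weeks before enrollment". Examination must also place the core pain area in the lumbar erector spinae, and consent is required. Nothing in the patient criteria mentions neuromuscular disease.

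For controls the text reads "The control group is healthy people of the same age group as the case group in the corresponding research part", and they must be "without lumbocrural pain symptoms and a history of neuromuscular diseases, who voluntarily signed the informed consent form". The history requirement is attached to neuromuscular disease; the pain requirement carries no period.

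Section 2.2.2 then gives one exclusion list and says of it: "The contents of the case group and the control group are consistent, and the three parts of the experiment are identical". The only stated exception is that item (h) is absent in Part 2. Items (a) to (h) do not name neuromuscular disease.

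Section 2.5.2 fixes the Part 1 primary analysis: "The primary comparison is between patients with LMS and healthy controls under the two stimulation conditions". Section 2.3.2 states that Part 1 involves no random allocation between the groups.

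**The concern.** In a comparison of patients with healthy people, nothing is balanced by randomisation. Comparability rests mainly on who is let in. A health condition that bars entry to one group and not the other becomes a possible explanation for any difference found.

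The item matters for this outcome. The fNIRS channels in 2.5.2 cover the prefrontal, supplementary motor, primary motor and somatosensory association cortex, and a history of neuromuscular disease could plausibly alter sensorimotor responses. As written, a patient with such a history may enter and a control may not. A group difference arising in this way would be read as a feature of lumbar muscle strain.

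The same control definition serves Part 3, where 2.4.3 and 2.8 use healthy participants as the reference for fNIRS and biomechanical responses, including muscle tension.

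A second, smaller matter concerns the controls' pain criterion. The disease is defined by recurrence, yet controls are given no pain-free period, so a person between episodes could arguably qualify. The Discussion holds that chronic musculoskeletal pain alters cortical function; on that reasoning, such controls would pull the two groups together.

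**Working it through.** **Step 1: the criteria side by side**

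| Item | Patients | Controls | Source |
|---|---|---|---|
| History of neuromuscular disease | not mentioned | excluded | 2.2.1 |
| Back pain | required, recurrent, over 3 months | no symptoms, no period given | 2.2.1 |
| General health | no general requirement | must be healthy people | 2.2.1 |
| Exclusions (a) to (h) | apply | apply | 2.2.2 |
| Neuromuscular disease named in (a) to (h) | no | no | 2.2.2 |

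The first row is an asymmetry in a factor other than the disease under study. The second row is not: pain status is what defines the groups, so a missing period there is a loose definition and not unequal screening.

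**Step 2: do the shared exclusions close the gap?**

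Item (d) covers "Complicated with non-soft tissue chronic injury diseases such as lumbar intervertebral disc herniation, spinal stenosis and intraspinal lesions", which is structural spine disease. Item (f) includes "Malignant tumors, acute infectious diseases, severe skin diseases, rheumatism and immune diseases" and may remove some immune-mediated neuromuscular conditions. Item (g) may remove patients on other treatment. Each narrows the gap; none names the category.

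**Step 3: can the bias be sized?**

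The shift in the patient mean would be the share of affected patients multiplied by their average departure from the other patients. The documents give neither quantity, so no figure follows.

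**Step 4: what dilution among controls could cost, as an assumed range**

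Inputs from 2.8: f = 0.286, alpha 0.05, target power 0.80, 12 per group, and 15 after 20% attrition. The inflation reproduces: 12 / (1 − 0.20) = 15. The 12 itself depends on software settings that are not stated. Assuming correlation 0.5, the group-by-condition interaction needs 14 per group with two measures and 11 with three.

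Assumptions: the interaction is the tested effect, N = 24 evaluable, correlation 0.5. With m measures and a proportional dilution a:

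lambda = (f × (1 − a))² × N × m / (1 − rho)

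For m = 2 and a = 0: 0.286² × 24 × 2 / 0.5 = 0.0818 × 96 = 7.85, on 1 and 22 degrees of freedom. Power from the noncentral F distribution:

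| Assumed dilution a | Lambda (m = 2) | Power (m = 2) | Power (m = 3) |
|---|---|---|---|
| 0 | 7.85 | 0.76 | 0.85 |
| 5% | 7.09 | 0.72 | 0.81 |
| 10% | 6.36 | 0.67 | 0.77 |
| 20% | 5.03 | 0.57 | 0.66 |

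If all 30 participants are evaluable, 20% dilution takes power from 0.86 to 0.68 (m = 2) or from 0.93 to 0.77 (m = 3). Here a is the share of controls who respond exactly as patients do; a weaker resemblance costs less. The table bears on the secondary clarification only. The neuromuscular point does not rest on it.

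**The case against.** The strongest reply is that the gap is small. Patients must satisfy a diagnostic standard that is not reproduced in the article and may itself rule out other causes of pain. Their pain must be localised on examination. Section 2.6 uses history, examination and imaging to screen out contraindications, and Table 2 schedules an X-ray, a specialised examination and a clinical diagnosis. Items (d), (f) and (g) will catch some cases. Section 2.4.3 also hints at why the item sits with controls: there they stand for people with intact lumbar muscles. All of this stands as narrowing the gap. None of it makes the written criterion bind patients, and no reason is given for applying it to one group.

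A reader might go further and infer that controls need only be free of back pain on the day, or that the groups are unequally screened in general. The text does not support either. Controls must also be healthy people and pass (a) to (h), the exclusion list is expressly common, and the difference is one named item. The article gives no time frame for the pain criterion, so reading it as current pain only is an interpretation.

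It is also fair to say that a look-back period is a detail a condensed article may leave to the full protocol, and that its absence can weaken a true contrast but would not by itself create a false one. That is why it is offered here as a clarification.

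**Conclusion.** The point holds for one criterion. As written, a history of neuromuscular disease excludes controls and not patients, in a primary contrast without random allocation and in the healthy-reference comparisons of Part 3. The primary ODI analysis in Part 3 compares two randomised patient groups drawn under the same criteria and is untouched.

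The size of any bias is unknown. A reader might be tempted to convert f = 0.286 into a between-group difference (2 × 0.286 = 0.57) and express one outlying patient as a share of it. That would not be sound: the prevalence and the offset would both be invented, and the same f cannot be read as a between-group effect there and as an interaction effect in the power figures.

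The missing pain-free period is secondary. Its possible cost is the assumed range shown above, which depends on the interaction being the tested effect, correlation 0.5, and a share of controls responding like patients that the documents do not supply.

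**What to change.** Move the history of neuromuscular disease from the control definition in 2.2.1 into the shared exclusion list in 2.2.2, so that it binds patients and controls alike in Parts 1 and 3. Because that list also governs Part 2, say whether the item applies there, as is already done for item (h). If the one-sided rule is deliberate, give the reason and treat it as a limit on interpreting the patient-versus-healthy contrasts.

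As a secondary clarification, state the period for which controls must have been free of low back pain, and ask about it at the medical history already collected (2.5.1 and Table 2). The length is the sponsor's choice.

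The cost is two eligibility lines, one screening question and a few more screen failures. It should be done before enrolment; a later repair would mean dropping participants from Part 1 groups of 15.
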